## Abstract

**Background:**

World Health Organization (WHO) recommends hospitalisation and injectable antibiotics for clinical sepsis / possible serious bacterial infection (PSBI) in young infants up to two months of age. However, some young infants with low-mortality risk signs of PSBI may not require hospitalisation, for which evidence needs to be generated.

**Methods:**

This is a protocol for a multicentre, individually randomised, open-label trial that will be conducted in seven sites in six countries Bangladesh, Ethiopia, India (two sites), Nigeria, Pakistan and Tanzania. All sites will use this common protocol with the same study design, inclusion of participants, intervention, comparison, and outcomes, as well as quality control and analysis procedures to contribute to the overall sample size. All young infants (age <60 days) presenting at study hospitals with any single low-mortality risk sign (high body temperature ≥38°C, severe chest indrawing, or fast breathing of ≥60 breaths per minute in <7 days old infants) will be randomised to either outpatient care with injectable gentamicin for two days and oral amoxicillin for seven days (intervention) or inpatient care with injection gentamicin plus injection ampicillin along with supportive treatment, where needed, for seven days (control). We plan to enrol 7000 eligible young infants, 3500 infants in each of the two study arms. A trained and standardised independent outcome assessor will visit all enrolled cases on days two, four, eight and 15 post-randomisation to assess the study outcomes in both intervention and control groups. The primary outcome of poor clinical outcome, defined as death within two weeks of initiation of treatment, deterioration during the 7-day treatment period, or persistence of the presenting sign at the end of the 7-day treatment period, will be compared to assess if the outpatient treatment leads to superior or at least non-inferior clinical outcome than inpatient treatment. The selected sites have extensive research experience. The methods and all study procedures will be harmonised through central training of research staff by WHO, standardisation exercises for clinical signs, central data coordination centre and internal and external monitoring. Continuous evaluation of the enrolment by the sites will be carried out through regular calls, databased monitoring, and site visits by WHO monitors. This trial has received ethical approvals from the WHO and local site institutional ethics committees.

**Discussion:**

If the results show that young infants with any single low-mortality risk PSBI sign can be effectively and safely treated on an outpatient basis, it may substantially increase access to treatment for infants and families with poor access to health facilities. It may also reduce the human, financial and material costs to the health system and allow the currently overloaded health facilities to focus on more critically ill infants. This evidence will contribute toward making a case for reviewing the current WHO PSBI management guideline.

**Registration:**

International Standard Randomised Controlled Trial Number ISRCTN44033252.

Neonatal mortality has substantially reduced over the last few decades, but an estimated 2.4 million neonatal deaths still occur worldwide annually, accounting for 47% of under-five deaths [1]. Neonatal infections account for over 35% of all neonatal deaths in South Asia and sub-Saharan Africa [2]. The World Health Organization (WHO) Integrated Management of Childhood Illness (IMCI) algorithm classifies neonates and young infants with clinically suspected sepsis as “Possible Serious Bacterial Infection (PSBI)” [3]. This classification is based on seven clinical signs – fast breathing (≥60 breaths per minute) in 0-6 days old babies, severe chest indrawing, high body temperature (≥38°C), low body temperature (<35.5°C), not able to feed at all or not feeding well / stopped feeding well, convulsions, and movement only when stimulated or no movement at all [3]. WHO guideline recommends that young infants with any sign of PSBI should be managed in a hospital with injectable antibiotics and supportive care [4]. When referral to a hospital is not feasible, the WHO guideline recommends further classification of these infants into those who are critically ill (**Box 1**) and those who have a clinical severe infection (CSI) [5]. CSI can be managed on an outpatient basis with injectable gentamicin for two or seven days and oral amoxicillin for seven days based on clinical trials from Africa [6,7] and Asia [8,9].

Box 1Sub-classification of children with signs of possible serious bacterial infection when a referral is not feasible [5].Critical illness• convulsions• not able to feed at all• no movement at allClinical Severe Infection
*Low-mortality risk signs*
• high body temperature (≥38°C*)• severe chest indrawing• fast breathing of ≥60 breaths per minute in <7 days old infants
*Moderate-mortality risk signs*
• low body temperature (<35.5°C*)• movement only when stimulated• not feeding well / stopped feeding well*Thresholds based on axillary temperature.

Several countries have now adopted the WHO PSBI management guideline [5]. Implementation research in several countries in Africa and Asia on the WHO PSBI guideline has demonstrated that this guideline can be scaled up and that outpatient treatment is safe and effective when hospitalisation is not feasible [10-22]. It is estimated that 8%-12% of all young infants had at least one episode of PSBI within the first two months of life. Overall, approximately a quarter to half of the sick young infants in different settings accept hospital referrals [6,8,23]. However, hospitalisation also has risks, particularly that of nosocomial infections, including those from multi-drug resistant pathogens [24-27]. Therefore, only those young infants with signs of PSBI who have a favourable benefit-risk ratio should be hospitalised. Secondary observational analyses of AFRIcan NEonatal Sepsis Trial (AFRINEST) [6,7] data showed that some of the more common clinical signs of PSBI are associated with relatively low mortality [28]. Specifically, having only fever (temperature ≥38°C) in infants 0-59 days of age, only severe chest indrawing in infants 0-59 days of age, or only fast breathing in infants 0-6 days of age had relatively low case fatality risk (CFR) of 0.8%, 0.9% and 2.0%, respectively [28] as compared to movement only on stimulation (CFR = 4%) or low body temperature (CFR = 11.0%) which had higher mortality. Infants presenting with multiple signs of CSI (two or more) also had a moderate risk of mortality (CFR = 5.7%). As expected, signs of critical illness were associated with a very high risk of death (convulsions, CFR = 11.3%, unable to feed at all, CFR = 22.9% and no movements at all, CFR = 25.0%).

An important implication of these findings is that young infants with signs associated with a relatively lower risk of mortality (fast breathing with ≥60 breaths per minute in 0-6 days of age, or temperature ≥38°C or severe chest indrawing in 0-59 days of age) may not require a referral for inpatient treatment in a hospital for one week per current WHO guidelines. If infants with low-risk signs of PSBI could be managed at the outpatient level, it may reduce the referral for hospitalisation by over 70%. On the other hand, infants who have the other signs of CSI (stop feeding well, movements only on stimulation, low body temperature), with multiple signs of CSI, as well as those who have a critical illness, are at a high risk of mortality [28] and may have a more favourable benefit-risk ratio for hospitalisation.

When mortality data from AFRINEST were analysed by place of treatment for all infants classified as PSBI, CFR was higher in hospitalised young infants as compared to infants treated on an outpatient basis when they refused referral for the same signs of CSI [28]. The overall CFR for young infants with CSI treated at the hospital was three times higher (6.5%) compared to those treated on an outpatient basis (1.9%) [28]. Nevertheless, due to the observational nature of the AFRINEST study and specifically that infants who refuse referral may be systematically different from those who accept, the findings cannot be considered causal. Therefore, there was a need to evaluate this in a randomised controlled trial.

The primary objective of this trial protocol is to measure the effect of outpatient treatment on poor clinical outcomes compared with inpatient treatment in young infants 0-59 days old with only one low-mortality risk sign of CSI. We hypothesise that the majority of infants with a single low mortality risk sign of CSI do not benefit from hospitalisation.

## METHODS

### Research question

Among young infants, 0-59 days of age with only one low-mortality risk CSI sign presenting to the outpatient / emergency department of a hospital (population), does outpatient treatment with injectable gentamicin for two days and oral amoxicillin for seven days (intervention), compared to the currently recommended inpatient hospital treatment initiated with injectable ampicillin and gentamicin and supportive care for seven days (control), result in lower rates of poor clinical outcome (death within two weeks of initiation of treatment, deterioration during the 7-day treatment period, or persistence of the presenting sign of CSI at the end of the 7-day treatment period) (outcome)?

### Study design, setting and sites

This will be a multicentre, individually randomised, controlled, open-label, two-arm trial. The study will be conducted in seven sites in six countries Bangladesh, Ethiopia, India (two sites), Nigeria, Pakistan and Tanzania (**Table 1**).

**Table 1 T1:** Details of the study sites*

Study site	Description
Bangladesh	The study will be conducted in four hospitals. Zakaiganj Upazila Health Complex (ZUHC), Zakiganj (primary / public), Sunamganj District Hospital (SDH), Sunamganj (secondary / public), Moulvibazar District Hospital (MDH), Moulovibazar (secondary / public), and Habiganj District Hospital (HDH), Habiganj (secondary / public) in Sylhet. ZUHC has six paediatric beds and one radiant warmer, SDH has 14 beds, one incubator and three warmers, MDH has 17 beds and 17 warmers, HDH has 11 beds and 11 warmers in their Neonatal Intensive Care Units (NICU) / Special Neonatal Care Units (SNCU) respectively. All are functional 24 h a day. Except for ZUHC, all hospitals have trained paediatricians, but none have a neonatologist. Oxygen is available 24 h a day through cylinders.
Ethiopia	The study will be conducted in five hospitals. One named Tirunesh Beijing Hospital (secondary / public) in Addis Ababa, and four in the Oromia region named Bishoftu Hospital (secondary / public), Adama Hospital (secondary / public), Batu Hospital (General Hospital), Asella Hospital, Asella (Referral Hospital). Tirunesh Beijing Hospital has 22 beds and 17 incubators / warmers, Bishoftu Hospital has 15 beds and 17 incubators / warmers, Adama Hospital has 53 beds and 11 incubators / warmers, Batu Hospital has 18 beds and two incubators / warmers and Asella Hospital 40 beds and eight incubators / warmers in their NICU/SNCU respectively. All are functional 24 h a day. All hospitals have trained paediatricians, but none have a neonatologist. Oxygen is available 24 h a day through cylinders.

### Participants

All young infants 0-59 days old, presenting to outpatient clinics or emergency departments of participating hospitals, and living in a geographic area where follow-up for 14 days can be accomplished will be considered for inclusion in this study if they have only one of the following low-risk signs of PSBI: 1) body temperature ≥38°C, or 2) severe chest indrawing, or 3) fast breathing (≥60 breaths per minute) in <7 days old infants.

Infants will be excluded if they have any of the following: 1) weight <2 kg at the time of presentation (if age at screening is less than 10 days) or weight for age<-3z, or 2) signs of critical illness (no movement at all, unable to feed at all, convulsions), or 3) signs of CSI associated with a moderate risk of mortality (stopped feeding well, movement only on stimulation, low body temperature <35.5°C or two or more of the six signs of CSI), or 4) any sign suggestive of another serious illness/condition, such as major congenital malformations, severe jaundice, conditions requiring major surgery, meningitis, bone or joint infection, severe dehydration, hypoxaemia, etc., or 5) the appearance of low-mortality risk signs in the first 24 hours of life, or 6) hospitalised for any illness in the previous two weeks, or 7) prior use of injectable antibiotics in the last two days for the same illness except for pre-referral administration, or 8) previously included in this study or currently included in any other study.

### Intervention

Outpatient treatment with injectable gentamicin (once daily) for two days plus oral amoxicillin (twice daily) for seven days.

### Control

Inpatient antibiotic treatment initiated with WHO recommended antibiotic regimen – injectable ampicillin (twice or thrice a day, depending on age) plus injectable gentamicin (once daily) along with other supportive care for 7-10 days.

One of the possible reasons that outpatient care was observed to be better than hospital care in previous studies might be the poor quality of care in hospitals. In this study, we would like to reduce this factor as far as practically feasible. This means that the quality of care at the study hospitals will be reviewed against the WHO pocketbook for hospital care for children [4] and will be improved using quality improvement approaches to ensure a “minimum” quality of hospital care. Efforts to improve the quality of care will also be made at outpatient facilities.

### Screening and enrolment

Young infants up to two months of age in the outpatient or emergency department will be examined, triaged and stabilised by the consulting paediatrician or physician of the participating hospital. This process followed as part of regular facility procedures is referred to as ‘pre-screening’. If the paediatrician / physician observes signs of CSI (**Box 1**) during their initial assessment and the clinical condition of the infant is stable, the infant will be assessed by the study screening, enrolment and randomisation team (**Box 2**). After the consent has been obtained for screening, a study nurse / physician will screen the sick young infants in the outpatient or emergency department of the participating hospital, and information will be captured on the case report form (screening and enrolment form). Those who fulfil the above-mentioned inclusion criteria and do not have any exclusion criteria will be enrolled after confirmation of clinical signs by the treating physician after obtaining consent from the parents or caregivers. The study nurse / physician will fill out the appropriate case report form at this stage. Infants who are not eligible for enrolment will be managed as per the treatment protocols of the hospital.

Box 2Responsibilities of study teams.Screening, enrolment and randomisation team• obtain consent for screening and perform screening of all young infants presenting at the outpatient or emergency department according to inclusion and exclusion criteria.• communicate with the hospital nurse / physician to validate clinical findings.• fill screening case report form.• for enrolment in the trial communicate with the hospital nurse / physician, obtain consent for enrolment and fill the required case report form, complete randomisation process and assign treatment arm as inpatient and outpatient, share this information with study coordinators.• share information about enrolled and non-enrolled cases with coordinators.Treatment documentation team• obtain information about inpatient from medical record and outpatient treatment from caregivers from days 1-7.• fill the required case report forms.Independent outcome assessment team• assess all enrolled infants on day 2, 4, 8 and 15.• communicate with hospital physician/nurse or study coordinator to confirm findings.• fill the required case report forms.• in case of serious adverse event, fill the required case report form.• for critically ill infants, obtain the survival status after 14 days of initiation assessment and complete the required case report form.Data management team• check data after completion by each team regularly.• clean data and upload cleaned data on central data management site on regular basis.

See the study approach for screening, enrolment and randomisation in **Figure 1** and the implementation strategy in **Table 2**. In addition, study information in terms of objectives and procedures will be posted in the labour and delivery wards, antenatal care clinics and postnatal clinics in the participating hospitals.

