### Outcome assessment

The proposed trial cannot be blinded due to the nature of the treatment. It is, therefore, important to incorporate measures to reduce potential measurement bias in the design of the study. We will use independent outcome assessors (IOA), who will be trained nurses or physicians or clinical field workers and will be independent of the enrolment and treatment to evaluate study outcomes. IOAs will be trained in standard management and study procedures. Outcome assessment will be carried out by independent outcome assessors (IOAs) and members of the outcome assessment team, who will visit all enrolled young infants on days 2, 4, 8 and 15 after enrolment. In the hospital arm, the outcome visits on days 2 and 4 will be done in the hospital, while the days 8 and 15 visits will be done at home (or in the hospital or where ever the child may have moved to). In the outpatient arm, the outcome visit on day 2 will be done when the infant returns to the hospital to receive the day 2 gentamicin injection. The outcome visits on days 4, 8, and 15 will be done at home or where ever the infant may have moved to.

The IOAs will only ascertain outcomes per the criteria mentioned above under outcomes. A case will be considered a poor clinical outcome if the IOA confirms it.

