Our study has several strengths. First, it is a multicentre study to be conducted in six countries across Africa and South Asia with a fairly large number of patients. Therefore, results are expected to be generalisable across a wide range of low-resource setting contexts. Second, standardised training, supervision, oversight, and monitoring will be undertaken to ensure quality, consistency, harmonised trial procedures and implementation. Trained study staff will document treatment and follow-up enrolled cases in the trial. Outcome assessment by an independent assessor will minimise ascertainment bias. Supervisors will ensure that the protocol and standard operating procedures are followed, data are accurately collected, and the highest level of safety is provided. Third, in addition to regular site monitoring visits by study staff and investigators, the WHO monitoring and coordinating team in Geneva will be engaged to assist with close external monitoring of the study, including regular site monitoring visits to assess compliance with human subjects, other research regulations and guidelines, adherence to the study protocol and procedures, quality and accuracy of data collected, and quality of care and child safety. Fourth, strong collaboration across sites with monthly steering committee meetings with all investigators for early identification and resolution of issues and challenges will be undertaken. Finally, the study is being conducted in partnership with the local governments to ensure early buy-in and translation into policy.

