There are also a few limitations. First, no laboratory or radiological assistance will be available to assist with the diagnosis. While microbiological and / or other diagnostic aids may add improved specificity to the clinical diagnosis of PSBI, peripheral health centres in low-resource settings do not have access to these investigations, and young infants are typically diagnosed based on clinical criteria alone. Second, the blinding of intervention therapy is not possible. Third, there may be an element of subjectivity involved in the assessment of poor clinical outcomes based on the presence or absence of clinical signs. To reduce bias, independent assessors will conduct outcome assessments in both intervention and control groups in a standardised manner. Finally, a potential limitation could be strengthening hospital-based care in the study facilities from an ethical standpoint, which may differ from other facilities that don’t get such support, making the findings less generalisable.

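### Box 2 has the independent outcome team confirm its findings with hospital staff or the coordinator before the form is filled, which conflicts with the assessor independence that the Outcome assessment section relies on

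*Protocol article*

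**What the plan says.** The Outcome assessment section starts from the lack of blinding: "The proposed trial cannot be blinded due to the nature of the treatment". Its answer to measurement bias is a separate group of assessors who "will be independent of the enrolment and treatment to evaluate study outcomes". It then fixes who decides the endpoint: "A case will be considered a poor clinical outcome if the IOA confirms it".

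The Discussion leans on this arrangement twice. Among the strengths it states: "Outcome assessment by an independent assessor will minimise ascertainment bias". Among the limitations it concedes that "there may be an element of subjectivity involved in the assessment of poor clinical outcomes based on the presence or absence of clinical signs", and again names independent assessors as the remedy.

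Box 2 (in Screening and enrolment) gives the same outcome team this duty: "communicate with hospital physician/nurse or study coordinator to confirm findings". It stands after the duty to assess infants on days 2, 4, 8 and 15 and before the duty to fill in the forms. In the same box the enrolment team is to "complete randomisation process and assign treatment arm as inpatient and outpatient, share this information with study coordinators".

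**The concern.** The people named for confirmation are those from whom the assessor is meant to be independent. Hospital staff help give the treatment, and the coordinator receives the allocation. If their view is sought before the assessor's finding is on record, the recorded endpoint may already carry the opinion of someone who knows the arm and may have a stake in the infant's course.

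This matters more here than in a trial with a hard endpoint. Much of the composite rests on clinical signs at a visit, such as chest indrawing or reduced movement, where a second opinion can change the answer. It would matter most if the influence differed between arms, because the risk difference would then shift. Table 3 works with non-inferiority margins of 1.8 and 1.5 percentage points on a control rate of 6.0%, so there is little room for ascertainment that depends on arm.

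**Working it through.** This is a question of procedure. The plan states no figure to reproduce, so the check sets the relevant texts side by side.

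1. **Who is consulted.** Box 2 names the hospital physician or nurse, or the study coordinator. Table 2 lists hospital or study staff as treatment providers in both arms. Box 2 sends the allocation to coordinators. Every named contact is therefore involved in treatment or knows the arm.

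2. **What the consultation is for.** The stated purpose is to confirm findings, not only to pass on information for care. Box 2 gives the screening team a parallel duty to check its clinical findings with hospital staff. The Screening and enrolment text shows what that means: the treating physician confirms the signs that the study team found. The outcome bullet is built the same way, so the natural reading is that staff confirm the assessor's finding.

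3. **When it happens.** The bullets run assess, consult, fill in the form. The list is not expressly a sequence, but nothing in the article puts recording before contact or says whose view stands on disagreement.

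4. **Whether the arms differ.** Settings are from Outcome assessment and endpoint components from Study outcomes. Death counts throughout, up to day 15.

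| Visit | Inpatient arm | Outpatient arm | Non-fatal components that count |
|---|---|---|---|
| Day 2 | Hospital | Hospital | Critical-illness sign; other serious infection |
| Day 4 | Hospital | Home or elsewhere | As day 2, plus a new CSI sign |
| Day 8 | Home, hospital or elsewhere | Home or elsewhere | As day 4, plus persistence of the presenting sign |
| Day 15 | Home, hospital or elsewhere | Home or elsewhere | None |

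The text is explicit for the inpatient arm: "In the hospital arm, the outcome visits on days 2 and 4 will be done in the hospital". On day 2 both arms are seen at the hospital, and new CSI signs do not yet count. On day 8 the planned settings overlap. Day 4 is the visit where the settings clearly part and a new CSI sign is an event.

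5. **Size.** An estimate would need the share of findings changed by consultation in each arm, and in which direction. The document gives neither, and any assumed rate would determine the answer, so no figure is offered.

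**The case against.** The strongest reply is that the decision stays with the assessor. The Outcome assessment section says so, and nothing in the article lets hospital staff or the coordinator overrule the assessor. That stands. A reader might infer from Box 2 that the safeguard is undone or that staff can reverse an endpoint; the document does not support either inference.

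A second reply is that the bullet may mean the assessor confirms what staff have reported. This fits the rule that a case counts when the assessor confirms it. It also fits the Adverse events section, where staff contact the assessor about a serious event. The reading is possible, but it is the weaker one given the parallel screening bullet and the place of the duty before form completion.

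Third, staff contact is not confined to inpatients. The Follow-up section has outpatients return to hospital staff on days 2 and 4, although their day 4 outcome visit is at home. This limits the arm contrast to the setting of the day 4 assessment and how readily staff can be consulted there.

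Fourth, assessors see the arm themselves, the article discloses this, and training, quarterly standardisation and supervisor verification remain. These reduce error in reading signs but do not settle the order of consultation and recording.

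Last, the order of recording could be left to the manual of operations, which is not shown. Silence on that alone would be no finding. Here, however, the article prints an instruction that conflicts with its own safeguard.

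**Conclusion.** The concern holds as an internal inconsistency. Box 2 directs the independent outcome team to confirm findings with people who help deliver treatment or know the allocation, while the Outcome assessment section offers independence from enrolment and treatment as the measure against bias. In an open-label trial with partly subjective signs, the instruction may weaken that safeguard.

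This rests on two readings: that confirmation runs from staff to assessor, and that the order of the bullets at least permits contact before recording. Both are the more natural readings, but neither is certain.

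The size is unknown. A reader might also infer that the instruction tilts the trial towards a non-inferiority conclusion. The document gives no basis for a direction: consultation could add or remove events in either arm, and so move the difference either way.

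**What to change.** Reword the Box 2 duty to match the Outcome assessment section. The assessor records and locks the findings before any contact with hospital staff or the coordinator about them, and then informs them so that care can be given. State that the primary endpoint uses only the assessor's locked entry, and that any later disagreement is logged by arm without changing that entry.

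The cost is one line in Box 2, a matching line in the manual of operations, and a time-stamped lock in the electronic form, which the sites already use for data capture. No extra staff are needed. The change concerns how the endpoint is recorded; communication for care remains.
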